As its name implies, the new approach is family-centered, which can be described as "placing the needs of the child, in the context of their family and community, at the centre of care and devising an individualized and dynamic model of care in collaboration with the child and family that will best meet these needs" [18]. The contents of the family-centered approach are based on the bio-ecological model of Bronfenbrenner [13] which reflects different child and contextual characteristics, and the interaction between these, influencing the development of the child. The model has been described as a promising framework for providing support to children in a successful way that is integrated into community-based services [19]. In the family-centered approach, the bio-ecological model is reflected in five different domains which are to be discussed with parents during each routine well-child visit and which concern the broad developmental context of the child. In addition to its contents, the family-centered approach is aimed at building a trusting and supportive relationship with parents in order to stimulate disclosure by and empowerment of the parents, and thus to enhance the positive psychosocial development of the child.

The family-centered approach seems to be a promising method for accurately monitoring psychosocial development, and the context in which infants grow up, in a way that enhances psychosocial development and early intervention if needed. In earlier research by Tan [20], internal validity and reliability of the family-centered approach were rated satisfactory. Furthermore, it was assessed that some domains of the family-centered approach showed a medium-significant correlation with the stress experienced by parents and family needs. The predictive value of the family-centered approach for identification of (risks for) social-emotional problems, along with the external validity of the five domains separately, were not studied by Tan, and is therefore still unknown.

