### Outcome measurements

There will be several primary outcomes from this study. The first of these will be the proportion of psychosocial problems identified by the CHPs in both the intervention and control regions. When the child is aged 2 to 14 months, the focus will be on social-emotional development, for children of 18 months of age behavioral problems will be taken into account as well. A second primary outcome will be the predictive value of CHPs' identifying psychosocial problems when a child is between 2 and 14 months old, and later at 18 months, in both the intervention and control conditions. The last primary outcome will be the concordance between the risk and protective factors as assessed by CHPs using the family-centered approach domains (Competence of the primary caretaker, Role of the partner, Social support, Perceived barriers or life events within the care giving context of the child, and Wellbeing of the child) and the outcomes on standardized questionnaires filled in by the parents in the subsample regarding these domains.

The secondary outcomes in the study will be the degree to which the needs of the parents are met and their willingness to disclose their concerns.

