### Measurements

Social-emotional and behavioral development will be assessed by both the CHPs and the parents. CHPs will indicate during each routine well-child visit between the ages of 2 and 18 months whether psychosocial development is fine, not optimal (but no extra care is needed), or whether there is a problem, indicating that an additional activity is needed. The definition of an additional activity is used to assess whether risks for or actual psychosocial problems exist. From 2-14 months, parents in the subsample of the study will assess the social-emotional development of their children by filling in the Ages and Stages Questionnaire Social Emotional (ASQ-SE) [25,26], an internationally validated questionnaire containing 22 to 29 items for children aged 3 to 60 months. When the child is 18 months of age, all participating parents will fill in the Child Behavioral Checklist (CBCL) 1.5-5, an internationally validated instrument containing 100 items that assesses psychosocial problems [22,23].

The competence of the primary caretaker will be assessed by CHPs within the family-centered approach format by registering whether the competence is regarded as a protective factor, unknown, or a risk factor. Parents from the subsample will indicate their competence by answering 11 items in the Dutch Parental Stress Index (PSI) [27]. Furthermore, the Setting Self-efficacy subscale (14 items) of the Problem Setting and Behavior Checklist (PSBC), measuring the confidence of the primary caretaker in mastering problem situations [28], and the Parental Sense of Competence scale (PSOC), 16 items measuring the competence of the parent [29] will be used. With the SF-12, an abbreviated version of the 36-Item Short Form Health Survey [30,31], the health status (physical and mental) of the parent will be assessed.

The role of the partner will be assessed by CHPs by indicating whether the role can be seen as a protective, unknown, or risk factor. Parents in the subsample of the study will assess the relationship between the partners using the 12-item General Functioning (GF) subscale of the McMaster Family Assessment Device (FAD) that addresses the emotional relationships within families [32,33]. Furthermore, having a baby and the effect on the relationship between the partners will be assessed using the subscale "relationship" of the Dutch Parental Stress Index (5 items) [27].

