### Statistical analyses

To compare the baseline characteristics of the participants in the intervention and control regions, chi-squared tests for categorical variables and t-tests for continuous variables will be used. If the intervention and control regions differ regarding the background characteristics of the children, appropriate multivariable analyses will be done using standard and logistic regression analyses to adjust for these differences.

Regarding the primary outcomes of the study, the following analysis will be performed. First, we will compare the proportion of, and risks for psychosocial problems identified by the CHPs in both the intervention and control conditions when the child is between 2 and 14 months of age and when the child is 18 months of age, using chi-squared tests and logistic regression analysis to correct for potential differences between regions. Second, we will assess the sensitivity, specificity, and the positive and negative predictive values of social-emotional and psychosocial problems identified by CHPs in both conditions, using the ASQ-SE [25,26] for children aged 2-14 months from the subsample and using the CBCL [22,23] for all participating children when the child is 18 months of age. Third, we will compare kappas as a measurement of agreement between the protective and risk factors assessed by the CHPs, and relevant reference questionnaires as filled in by the parents from the subgroup.

For the secondary outcomes of the study, we will compare met and unmet needs of the parents between conditions using independent t-tests and multivariate regression analysis to correct for potential differences in background characteristics. The level of willingness to disclose concerns will be compared using ordinal regression analysis.

Data will be analyzed using SPSS 18.0. The significance level is set at .05.

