In interpreting results in terms of the predictive value of the CHPs' identification of the psychosocial development of children, it is important to note that we will be using the ASQ-SE for children younger than 18 months and the CBCL 1.5-5 for children aged 18 months as the "gold standard." We should note, however, that this gold standard does not fully reflect the judgment of the CHPs, which is also based on clinical experience. In an ideal situation, we should also gather information from independent experts in order to have a possibly more objective and informative measurement of psychosocial development. This will not be part of our study due to the large numbers and the time-consuming method that would involve.

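### Flags at 2-14 months are to be judged by the same-age ASQ-SE, but the sample size assumes CBCL confirmation, and no stated analysis links an early flag to the child's 18-month CBCL

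*Protocol article*

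**What the plan says.** All references are to the protocol article.

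- **Outcome measurements** defines the second primary outcome as the "predictive value of CHPs' identifying psychosocial problems when a child is between 2 and 14 months old, and later at 18 months", in both conditions. It names no reference standard for either rating.
- **Statistical analyses** gives the measures: "we will assess the sensitivity, specificity, and the positive and negative predictive values of social-emotional and psychosocial problems identified by CHPs". It then gives the references: "using the ASQ-SE [25,26] for children aged 2-14 months from the subsample and using the CBCL [22,23] for all participating children" at 18 months.
- **Potential limitations** restates the reference by age: "we will be using the ASQ-SE for children younger than 18 months and the CBCL 1.5-5 for children aged 18 months".
- **Measurements** says who completes what. The ASQ-SE is limited to the interviewed families: "From 2-14 months, parents in the subsample of the study will assess the social-emotional development of their children". The CBCL is not: "When the child is 18 months of age, all participating parents will fill in the Child Behavioral Checklist (CBCL) 1.5-5".
- **Procedure** has CHPs record their finding at every routine visit from 2 to 18 months for all participants. A flag is a rating that calls for an additional activity.
- **Sample size and power calculation** takes 22-23% from an earlier study of children aged 2-4 years, where it is the share of identified children with a clinical CBCL score. It sets 42% as the target, asks for 85 cases per condition, and counts cases from an expected 10% flagged between 2 and 14 months.
- **Background** names as still unknown "The predictive value of the family-centered approach for identification of (risks for) social-emotional problems".

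**The concern.** The sample size and the analysis describe different quantities. The sample-size section assumes that early-flagged cases are confirmed by the CBCL. In this study the CBCL is completed only at 18 months, so a case flagged at 2-14 months can be CBCL-confirmed only by linking the early flag to the later score. The two sections that name the reference standard do not describe that link. They assign the ASQ-SE, in the subsample, to the younger ages.

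Two things are at stake. First, the 22% to 42% assumption has no matching analysis, and the article gives no expected ASQ-SE confirmation rate to replace it. Second, a flag covers risks as well as existing problems. A questionnaire at the same age can show whether a problem is present, but it is weak evidence on whether a risk flag was right. An analysis that follows the text as written could finish without reporting whether early-flagged children are the ones with problems at 18 months, or what share of children with problems at 18 months had been flagged before.

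**Working it through.** **1. Reproduce the stated 85.** Inputs: p1 = 0.22, p2 = 0.42, power 80%, alpha .05 (Sample size and power calculation). Two-sided testing and equal groups are assumed, because the article states neither.

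n = [1.960 × √(2 × p̄ × (1 − p̄)) + 0.842 × √(p1(1 − p1) + p2(1 − p2))]² / (p2 − p1)², with p̄ = 0.32

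- 2 × 0.32 × 0.68 = 0.4352
- 0.22 × 0.78 + 0.42 × 0.58 = 0.4152
- n = (1.293 + 0.542)² / 0.04 ≈ 84.2, rounded up to **85 per condition**

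The stated figure reproduces. Power at n = 85 is 80.4%.

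**2. Reproduce the yield, per condition.** 2,500 × 0.70 = 1,750 families. 1,750 × 0.10 = 175 early cases. The article then gives 121 cases agreeing to interview, and 121 × 0.70 = 84.7 with complete data (175 × 0.70 × 0.70 = 85.75 without intermediate rounding). So about 85 interviewed cases per condition are expected, which matches the requirement.

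**3. Which reference do those 85 have?**

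| CHP rating | Reference stated | Who has it | Basis of the power figure |
|---|---|---|---|
| 2-14 months | ASQ-SE, same age | Interviewed cases and matched controls | Cases are counted here, but the rates are CBCL-confirmed |
| 18 months | CBCL, same age | All participants | CBCL, but cases are not counted here |
| 2-14 months against the 18-month CBCL | None stated | All participants with a CBCL | Closest match to both the rates and the case count |

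The figure of about 85 per condition applies to the early PPV only. Early sensitivity, specificity and negative predictive value also use the matched controls (242 invited). The 18-month analysis uses up to 1,750 per condition before attrition.

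**4. What the missing pairing would offer.** Neither the CHP records nor the CBCL depends on the interview, so all 175 early cases per condition are candidates. The article gives no CBCL return rate, so it is varied here.

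Power = Φ{[0.20 × √n − 1.960 × √0.4352] / √0.4152}

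| Assumed CBCL return among early cases | n per condition | Power, 22% vs 42% |
|---|---|---|
| 48.6% | 85 | 80.4% |
| 50% | 87-88 | 81-82% |
| 60% | 105 | 88.0% |
| 70% | 122 | 92.2% |
| 80% | 140 | 95.2% |

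The 95% half-width for the difference, 1.96 × √(0.4152 / n), is 13.7 points at n = 85 and 11.4 points at n = 122.

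**5. How far this depends on the 10% rate.** Time frame calls that rate uncertain. At 70% return, 85 cases need 85 / 0.70 ≈ 121 early flags per condition, and 121 / 1,750 ≈ 6.9%. Below that flag rate, this analysis also falls under about 80% power.

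**The case against.** **A reader might infer that early flags are certain never to be tested against the CBCL.** The text does not support that. The clause on the CBCL dates the questionnaire; it does not say that only the 18-month rating is compared with it. Outcome measurements leaves the reference open, and the CBCL-based power calculation on 2-14 month cases suggests that the later comparison may have been intended. What stands is that the pairing is not stated and that the two places naming a reference point the other way.

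**A reader might infer that the whole predictive-value outcome rests on about 85 cases, or that the sample size is wrong.** Neither follows. The count is per condition and concerns the early PPV, and the arithmetic is correct for its inputs.

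**Same-age comparison is a legitimate accuracy design.** It answers whether CHPs recognise existing problems, which is part of the study's hypothesis. This stands, and the ASQ-SE analysis should stay.

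**The later comparison has its own bias.** A flag leads to an additional activity, and the CBCL follows 4 to 16 months later. If that care works better in one condition, the later PPV there falls for a good reason. A child wrongly flagged early may also develop a new problem by 18 months and count as confirmed. This stands in full: the later PPV is not a strict lower bound for correct early flags, and its comparison between conditions may be biased.

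**A journal article may leave such detail to a fuller document.** That would answer a mere omission. Here the article states the reference by age in two places and powers the study on a different pairing, so the conflict lies within the text shown.

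**Conclusion.** The point holds as an inconsistency between the stated analysis and the sample-size basis, together with an unstated pairing that matters for the study's purpose. As specified, the early PPV measures same-age agreement with the ASQ-SE in about 85 cases per condition, and the CBCL-based 80% power does not describe it. Linking early flags to the 18-month CBCL would use data already planned for all participants. It would reach at least the stated power if about half of flagged families return the CBCL, and about 92% at 70% return.

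Those figures rest on three assumptions: 175 early cases per condition, the 22% and 42% rates carrying over from children aged 2-4 years to infant flags tested months later, and the assumed CBCL return. The article supports none of the three firmly, so the power figures are indicative. The conflict between the sections does not depend on them. The change should be made, but the point does not invalidate the design.

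**What to change.** 1. In Outcome measurements and Statistical analyses, state the reference questionnaire, its timing and the analysed group for each CHP rating. Bring Sample size and power calculation and Potential limitations into line, and say which PPV the 85 cases per condition are meant to serve.
2. Add an analysis that cross-classifies ever flagged at 2-14 months (yes/no) by CBCL clinical score at 18 months, in all participants with a CBCL. Report PPV, negative predictive value, sensitivity and specificity per condition.
3. Keep the ASQ-SE analysis as the same-age check.
4. State the limits with the new analysis: care after a flag can lower later CBCL scores, possibly more in one condition, and new problems can arise after a wrong flag. The difference in PPV between conditions should be interpreted with that in mind.

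The cost is wording and one further cross-tabulation on data already to be collected. No extra visit, consent or questionnaire is needed.

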## Discussion

This paper presents the design of a quasi-experimental study whose aim is to assess the added value and effectiveness of a new family-centered method designed to monitor psychosocial development and those factors which may influence psychosocial development in early childhood. Daily practice needs an evidence-based method to monitor psychosocial development and identify psychosocial problems at an early age, since this may contribute to early intervention, when needed, and thus to the wellbeing of the child and his/her family [6-8,12]. Internationally, the importance of early identification of psychosocial problems is acknowledged [39], and different questionnaires regarding psychosocial development have been developed and studied such as, for example, the Child Behavior Checklist (CBCL) and the Ages and Stages Questionnaire Social Emotional (ASQ-SE) [2]. However, there are no evidence-based methods, aimed at both the psychosocial development of the child as well as at the contextual risk factors, which can be integrated into routine well-child care, although Bright Futures has been described as promising [40]. The theoretical basis of the family-centered approach represents a promising start in supporting children and families in integrating with community-based services successfully [19], and takes into account both the difficulties and delicacies found in the early identification process. If the family-centered approach proves to be effective, its feasibility in routine care will be high because it has already been implemented successfully in routine care in the intervention regions.

### Strengths

We expect the findings of this large prospective quasi-experimental study into the daily practice of PCH to be very useful for practitioners and policymakers. Inclusion and exclusion criteria are set so as to highly resemble routine care in order to obtain generalizable findings. For the same reason, we will be investing a great deal in order to enhance the participation of all parents. For example, before the study started, we were able to focus media attention on the study in order to interest potential participants. Furthermore, in the information packet for parents, a small gift is provided to further spark the interest of the parents, and when we wrote the information flyer we made use of input from the CHPs so as to appeal to parents. For that part of the subsample in which an additional activity is to be carried out by a CHP, the parents will be informed by their own CHP and thereafter will be contacted by an interviewer who will visit the families at home. Interviewers are all well trained and have very good communication skills which should enhance participation of families. To further facilitate the participation of parents, we trained all the CHPs before the study started, interactively informing them how to motivate parents adequately and, if necessary, to remove any barriers felt by parents.

Besides evidence regarding the effectiveness of identifying the risks for psychosocial development, our study will also provide insight into whether parents experience the family-centered approach as truly family-centered. This insight may be very useful for the design of further training sessions for the CHPs. Furthermore, the evidence about whether parents feel free to disclose possible concerns to their CHP may provide interesting and important information. Disclosure by parents seems a sine qua non for the early identification of, and risks for, psychosocial problems. Parental concerns have even been shown to be as accurate as other screening methods such as questionnaires [14].

This study will prospectively monitor the development of a large number of children. Therefore, it will provide a wealth of information about the early development of infants and about factors within the child or those contexts which may influence psychosocial development in the first 18 months of life. With this structured way of monitoring psychosocial development at such an early age, we should gain more insight into the normal developmental pathways of children during the first 18 months.

### Potential limitations

This study also has some limitations. First of all, randomization will not be possible, since both the CHPs and parents are bound to their PCH regions. However, we will minimize contamination between regions, for example, through separate training sessions for the CHPs, by actively involving management of both the intervention and control regions, and by avoiding that CHPs work in regions of both the intervention and control condition.

Selection bias may also possibly influence the study's findings. To minimize this, we have taken several measures to promote the participation of all parents. As stated above, all the CHPs were instructed on how to pass information onto parents and how to use effective strategies to remove any barriers to participation, both in the overall study population and in the subsample of parents. For those parents who do not want to participate, the CHP will ask whether the parent would agree to share some background characteristics (age, gender, country of birth, and employment status of parents) and the assessment of the psychosocial wellbeing by the CHP when the child is 8 weeks of age. By collecting this information, comparisons between groups can be made to provide insight in the presence of potential selection bias.

One challenge in this study concerns the large number of participating CHPs who all need to comply with the study protocol. However, this reflects daily practice very well, which highly contributes to the generalizability of our findings. Moreover, to enhance the compliance of all CHPs, from the outset we will monitor all results very closely in terms of inclusion percentages and filling in information in the medical records of participating children. Results will be presented during team meetings. With close monitoring, we should be able to provide interventional action at an early stage if needed.

In interpreting results in terms of the predictive value of the CHPs' identification of the psychosocial development of children, it is important to note that we will be using the ASQ-SE for children younger than 18 months and the CBCL 1.5-5 for children aged 18 months as the "gold standard." We should note, however, that this gold standard does not fully reflect the judgment of the CHPs, which is also based on clinical experience. In an ideal situation, we should also gather information from independent experts in order to have a possibly more objective and informative measurement of psychosocial development. This will not be part of our study due to the large numbers and the time-consuming method that would involve.

